#### **1.2.2.3 Acute toxicity study data**

During preclinical animal studies, UC-781 was administered at high multiples (up to 345-fold) of the anticipated human exposure without significant toxicology. There was no evidence of systemic toxicity to UC-781 during single dose pharmacokinetic or dose ranging studies in rats (oral and intravaginal administration) and monkeys (oral, subcutaneous and intravenous administration).

#### **1.2.2.4 Repeated dose toxicity data**

In the repeated dose toxicity studies, there was little evidence of systemic toxicity; any incidences of local irritation are also below and in the Investigator's Brochure.

#### Oral dosing

5-day rat- Mild transient elevations in BUN, not associated with elevated creatinine.  
3/ grp, 6 groups  
(up to 1200 mg/kg/d)

28-day rat- Statistically significant difference in liver weight for the 2 highest dose groups (100mg/kg/day and 400mg/kg/day) compared to controls, but these were not associated with microscopic liver changes.  
10/ grp, 4 groups  
(up to 400 mg/kg/d)

#### Intravaginal dosing

7-day rat- No toxicity  
5/ grp, 4 groups  
(up to 110 mg/kg/d)

28-day dog- No systemic toxicity.  
3/ grp, 4 groups  
(up to 50 mg/kg/d) Local irritation-  
Erythema (3/3 in the mid and high dose UC-781 groups)  
Discharge (all UC-781 groups)  
Edema, severe (2/3 in the high dose group)  
Histopathology: atrophy, inflammation were actually observed with less frequency in the mid and high dose UC-781 groups than in low dose UC-781 and control groups.

#### Rectal dosing

28-day rat- Results pending

28-day rabbit- No systemic toxicity  
4/ grp, 6 groups  
(up to 2.5% gel) Final report pending

In addition, UC-781 showed no genotoxicity as determined in three standard test systems (Ames test, *in vitro* Chinese Hamster Ovary cells, and *in vivo* micronucleus test in mice.

#### **1.2.2.5 Irritation study data:**

##### Vaginal

In a 10-day rabbit vaginal irritation study, a 1% UC-781 gel formulation (equivalent to 3.33 mg/kg/day), a vehicle gel, or a 0.9% saline control was applied vaginally. A single observation of external vaginal erythema (scored as "Red" on grading system) was noted in 1/10 rabbits dosed with the 1% UC-781 gel, 1/10 rabbits dosed with the vehicle gel, and none of the rabbits dosed with the saline control. The erythema was not observed at any other timepoints in any of the groups. Histopathology results indicated minimal to moderate mixed inflammatory cell infiltrations, exudates, and edema in both the treated and control groups. The inflammatory response (mixed inflammatory cell infiltrations and exudates) was considered to have been due to repeated manipulation of the vagina since the responses in saline were increased in severity and incidence when compared to all other dose groups.

##### Penile

In a 7-day penile irritation study in rabbits a 1% UC-781 gel formulation, 3% UC-781 gel formulation, vehicle gel, or a 0.9% saline control was applied topically to the penis. Rabbits were treated twice daily for seven consecutive days. The test article, vehicle, or saline control was applied with a syringe to the mucosal area beneath the sheath and spread evenly over the penis with a glass rod. The two daily doses were separated by five to six hours. At approximately the same times each day, rabbits were collared (for about two hours after each dose) to prevent removal of the test materials via grooming. Results from this study indicated that UC-781 did not produce penile irritation at concentrations up to 3%, a dose level higher than that anticipated to be used during Phase 1 clinical trials.

#### Sensitization

UC-781 was shown to be a mild sensitizer in a guinea pig sensitization study. The objective of this study was to evaluate the potential of UC-781 to cause or elicit skin sensitization reactions (allergic contact dermatitis) via topical applications. The UC-781 carbomer gel formulations (1%, 3%, and 10%) were administered once during a dose range-finding screen. Based on results from the range-finding screen, the vehicle control gel, a positive control (100%- $\alpha$ -hexylcinnamaldehyde), and 10% UC-781 carbomer gel formulation were administered once weekly for three weeks during the induction phase. Following a two-week washout period, the groups began the challenge phase of the study which consisted of a single dose of test article. The positive control group from the induction phase received a 50%- $\alpha$ -hexylcinnamaldehyde in mineral oil during the challenge phase. Both the vehicle control and UC-781 groups from the induction phase received the 10% UC-781 carbomer gel during the challenge phase. A sensitization response was defined as a reaction in the UC-781 group greater than those seen in the vehicle or positive control gel animals at the challenge sites. The results indicated that 10% UC-781 carbomer gel is a mild sensitizer (2/20 animals had a score greater than 0.5).

#### **1.2.2.6 Safety study data in 0.1% and 1.0% UC 781 in pigtailed macaque:**

##### Vaginal

Two separate studies were undertaken: 1) 0.1% UC-781 vs placebo and 2) 1.0% UC-781 vs placebo. There were 6 animals in each treatment group. Each animal received 4 daily doses of study product. On day 5, there were no detectable levels of UC-781 in the serum of any of the animals. Colposcopic examinations of all animals were within the normal range. All pH measurements were within the normal range (4.0-8.0) for the vagina of the pigtailed macaque. However, 3/6 animals in the 0.1% UC-781 group had a transient drop in pH 30 minutes after gel application, but remained within the normal range.

[figure not shown]

When comparing vaginal microflora among the three treatment groups, there were no significant differences in the prevalence of either H2O2 producing lactobacillus or viridans streptococci in any study arm. Likewise, when comparing prevalence of the H2O2 producing microorganisms within treatment groups, no significant differences occurred. Furthermore the only constituent of vaginal flora shown to be affected by UC-781 was black GNR. The quantity of black GNR grown from vaginal swab specimens decreased on days 3 and 4 ( $p < 0.02$ ) after 0.1% UC-781 use. Following 1.0% UC-781 use, the quantity of black GNR decreased significantly ( $p < 0.05$ ) on days 4 and 5. By day 8, the growth titers had rebounded and were similar to baseline levels in both treatment groups.

#### Rectal

Two separate studies were undertaken: 1) 0.1% UC-781 vs placebo with a cross-over and 2) 1.0% UC-781 versus placebo with a crossover. There were 6 animals in each treatment group. Each animal received 4 daily doses of study product. On day 5, there were no detectable levels of UC-781 in the serum of any of the animals. All pH measurements were within the normal range (5.5-8.5) for the rectum of the pigtailed macaque. There were no significant differences between the two UC-781 test arms and the placebo regarding pre and post application pH. Within each treatment group, there were significant differences between pre and post-application rectal pH. Despite the acidic pH of the product and placebo, rectal pH increased significantly after application on all 4 days in the placebo group and on days 2 and 4 in the 0.1% UC-781 group. After 1.0% UC-781 rectal application a significant increase in pH was noted on day 3 only. Though there were transient pH shifts with product application, there were no significant differences between pH at baseline and follow-up in any group.

[figure not shown]

There was no statistically significant difference in the number of epithelial sheets or presence of blood/stroma in the rectal lavage specimens collected 2-4 hours after dosing. Semi-quantitative analysis of the prevalence of rectal microflora showed no significant differences in the prevalence of microflora when assessed daily, or pre and post-application of 0.1% or 1.0% UC781 or placebo. In addition, there were no significant differences in the prevalence of microflora at follow-up compared to baseline in either group. Rectal use of 0.1% or 1.0% UC781 did not significantly alter the presence of H2O2 producing *Lactobacillus* or viridans streptococci.

### 1.2.3 Clinical Research

The principles of clinical development drafted by Mauck et al can be seen in the UC-781 clinical program.

A Phase I clinical trial to evaluate the safety and acceptability of UC-781 in healthy, sexually abstinent women was conducted in Virginia. In this randomized, double-blind, placebo-controlled study, a total of 48 volunteers were enrolled at a single site and asked to apply placebo gel (N=12), 0.1% UC-781 (N=12), 0.25% UC-781 (N=12) and 1% UC-781 (N=12) intravaginally once per day for six days.

Subject participation in this first clinical study with UC-781 entitled, "Single and Multiple Exposure Tolerance Study of UC-781" (Protocol No. A02-083) occurred between August 2003 and March 2004. The study was designed to assess the safety and acceptability of three concentrations of UC-781 (0.1%, 0.25%, 1%) after a single dose and five additional consecutive daily doses administered to 12 women in each of the UC-781 dosage and placebo groups, a total of 48 women. Subjects were evaluated by pelvic exam with colposcopy after the first and sixth gel applications.

A total of 37 AEs were experienced by 8 (66.7%) participants in the placebo group, 5 (41.7%) in the 0.1% UC-781 group, 5 (41.7%) in the 0.25% UC-781 group and 4 (33.3%) in the 1.0% UC-781 group (Table 1). Only one of the eight moderate AEs was determined to have any relationship to a study product.

Participants' plasma samples were analyzed for UC-781 at baseline and after 6 applications of placebo gel, 0.1%, 0.25%, or 1% UC-781 gel. The lower limit of quantification (LLOQ) of the LC-MS bioanalytical assay was 2.5 ng/mL. There were no detectable levels of UC-781 in samples after treatment with placebo gel or 0.1% and 0.25% UC-781 gels. After six daily applications, two participants who were randomized to the 1% UC-781 gel group had plasma levels that were detectable but less than the LLOQ.

The key acceptability item was whether or not the subject indicated that she would buy the product if she needed protection against HIV and if the product she used were effective. All of the participants indicated that they would buy the product if proved effective with only one exception in the 0.1% UC-781 group.

Another Phase I study conducted at Emory University was started in October 2005 in order to assess the safety and acceptability of vaginal use of 0.1% and 0.25% UC-781 gel in sexually active HIV-uninfected women, and their male partners, and sexually abstinent HIV-infected women. The population will consist of 36 sexually active HIV-uninfected women and up to 36 of their male partners; in addition to 18 sexually abstinent HIV-infected women

The study will proceed in two stages. In Stage 1, sexually active HIV-uninfected women will be randomized to apply 0.1% UC-781 Gel, 0.25% UC-781 Gel or Control Gel intravaginally twice daily for 14 days. If safety data from stage 1 is acceptable with no evidence of UC-781 systemic absorption, the study will proceed to Stage 2. In Stage 2, sexually abstinent HIV-infected women will be randomized to apply 0.25% UC-781 Gel or Control Gel intravaginally twice daily for 14 days.

This Phase I study will continue the clinical development pathway for UC-781, progressing from the initial 6-day study of multiple concentrations in sexually abstinent women to a 14 day, twice daily application study using 0.1% and 0.25% concentrations in sexually active women. Because, the potential for absorption is higher with the 1% formulation, this 14-day study will involve the 0.1% and 0.25% UC-781 gel formulations only.

Recruitment is anticipated to take 6 months. Currently, there are 3 subjects enrolled into the trial. No serious adverse events have been reported.

Two additional Phase I studies are being developed in Thailand and Botswana. These studies will continue to evaluate the safety, acceptability, and toxicity data necessary to develop UC-781.

### 1.3 Rationale

Past studies have shown that vaginal products are often used rectally. Developing a safety profile for rectal use of the UC-781 vaginal microbicide is the safest course of action. Successful demonstration of safe and acceptable use of the UC-781 vaginal gel formulation rectally may lead to further clinical development of UC-781 gel for rectal use.

The decision to pursue clinical development of a candidate UC-781 gel formulation depends on multiple measures of safety, pharmacokinetics, and acceptability. The rationale for each endpoint is described in more detail in Section 2.1.

In order to discover the potential effects of UC-781 formulated for vaginal use when administered rectally, the study design involves 2 treatment stages: Treatment Stage 1, single dose rectal application of study gel in the clinic; Treatment Stage 2, outpatient self-administered rectal application of the study gel once daily for 7 days. After each treatment phase, subjects will have intensive clinical assessments.

Healthy volunteers will be studied due to the confounding effect of existing GI pathology with active infections, including HIV. Adults with a history of receptive anal intercourse will be recruited as one important population intended for future use of the UC-781 rectal gel formulation. Past sexual experiences with RAI will put the acceptability assessments in context. This multi-treatment design will establish an ideal dose and dosing regimen to proceed with clinical development.

## 2.0 STUDY OBJECTIVES AND DESIGN

### 2.1 Objectives

#### 2.1.1 Primary Objective

To evaluate the safety and acceptability of 0.1% and 0.25% UC-781 vaginal microbicide gel versus placebo when applied rectally.

Parameters to be studied include:

- Frequency of  $\geq$ Grade 2 adverse events

Rationale: Frequency of adverse events is always an objective in a Phase I study of an investigational product.

- Acceptability assessments

Rationale: The importance of determining acceptability in the early phases of microbicide development cannot be overstated. Making changes to a product earlier rather than later in development will reduce the total cost of drug development significantly and ultimately achieve the desired outcome, increased use of a product that would decrease the global burden of HIV.

In order to assess acceptability, questionnaires will be posted on a Web page that will be accessible only to study participants by entering a password. Web-based surveys have all the advantages of Computer Assisted Self Interview (CASI) over paper-and-pencil or interviewer-administered assessments, especially for sexual behavior. Advantages of using Web-based or CASI surveys include greater privacy and confidentiality, and increased likelihood that risky behaviors will be reported due to lack of self-presentation bias. The experience of colleagues at the HIV Center for Clinical Studies, in New York City, with these technologies has been extremely positive, even with participants who had never used a computer. This

technology also allows data entry directly into an electronic file, thus minimizing coding and entry errors. Core C, the MDP Data Management and Biostatistics Core, will program the questionnaires for secure posting on the Web.

**Baseline Behavioral Questionnaire (BBQ).** Prior to Visit 3, participants will be asked to respond to the BBQ. The content of the BBQ and the rationale for inclusion in the currently proposed study appear in Table 2.

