#### Design:

[figure not shown]

Participants will enter a screening period, which includes Visit 1 and if necessary a medication washout period.

Subjects who are deemed eligible after this screening period will return for a baseline evaluation (Visit 2), including clinical evaluation and mucosal specimen collection, as well as the Baseline Behavioral Questionnaire (BBQ). The BBQ will be administered by Computer Assisted Self-Interview (CASI). Subjects may complete the web-based CASI in the privacy of their own home. If a subject does not have access to the Internet, prefers to complete the BBQ at the study site, or requires assistance in using the CASI, he or she will be accommodated at the study site.

After completing Visits 1 and 2, eligible subjects will be randomized to one of three groups: 0.1% UC-781 gel, 0.25% UC-781 gel, or a placebo gel (12 per group). A subset of 9 subjects (3 from each group) will also participate in a pK sub-study, which will include 6 timepoints (Visit 3-pre, 0.25 hr, 2 hr, 4 hr, Visit 3A- 24 hr, and Visit 5- 1 day post-QD dose). During randomization, study staff will be notified if the participant is randomized to the pK substudy.

This study will involve 2 stages of treatment. **Each treatment stage is independent of the other. This study aims to examine the effects of 2 different dosing regimens, NOT cumulative safety over the both stages.**

Once randomized, subjects will return to the clinic (Visit 3), where a single dose of the study gel (Treatment Stage 1) will be administered after a preparatory Normosol-R pH7.4 enema. Within approximately 30 minutes, lavage, stool, sponge, and colorectal biopsy specimens will be obtained. Subjects will receive a safety follow-up phone call.

Subjects will return to the clinic for Treatment Stage 2 Clearance (Visit 4), in the week prior to beginning Treatment Stage 2. If given clearance, the subject may begin Treatment Stage 2.

In Treatment Stage 2, subjects will begin to self-administer once daily outpatient doses of the study gel for 7 days. Subjects will receive a follow-up safety phone call mid-way through

Stage 2. After completion of Stage 2 the subject will complete a Product Acceptability Questionnaire (PAQ) by CASI and return to clinic for evaluation and specimen collection (Visit 5). Subjects will receive a safety follow-up phone call.

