| H       | HIV Testing                      | By eligibility criteria, all participants will be HIV-negative. We will assess frequency of HIV testing and latest test occasion prior to enrollment in the study.                                                                                                                                                                                                                                                                                                                                                                                                                                      |
| I       | Rectal Microbicide Intentions    | To assess intentions to use a microbicide gel and a preparatory enema before RAI. This will allow us to detect pre-trial attitudes about such products and how they may affect later ratings.                                                                                                                                                                                                                                                                                                                                                                                                           |
| J       | Pleasure                         | Severy, et al.  stated that one of the main reasons people have sex is for pleasure. These items explore the effect of condoms on sexual pleasure. They will serve as baseline to compare pleasure ratings related to the different products used in the trials.                                                                                                                                                                                                                                                                                                              |

**Product Acceptability Questionnaire (PAQ)** The PAQ will be completed within the Visit 5 window after the completion of treatment stage 2, once the participant has had the opportunity to familiarize himself/herself with method of application, applicator, and product characteristics. The Product Acceptability Questionnaire includes both close-ended and open-ended questions (see Table 3)

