## 2.2 Study Design

This is a phase I randomized, blinded, placebo-controlled study of the safety and acceptability of the vaginal formulation of UC-781 gel, when administered rectally, to be conducted in 36 adults (12 per group) residing in the Los Angeles, CA area. All of the participants will be HIV negative. The study design is summarized in the Schema above and the Schedule of Events in Appendix I.

This study will involve 2 stages of treatment. Each treatment stage is independent of the other. **This study aims to examine the effects of 2 different dosing regimens, NOT cumulative toxicity over both stages.** Participants will undergo extensive evaluation during 5 study visits over an approximately 7-14 week period. In addition, acceptability assessments will be completed at baseline and Visit 5.

Interested participants will enter a screening period, which includes (Visit 1) and if necessary a medication washout period. Subjects, who are deemed eligible after this screening period, will return for a baseline evaluation (Visit 2), including clinical evaluation and mucosal specimen collection, as well as a baseline behavioral assessment (BBQ). The BBQ questionnaire will be administered by CASI. Subjects may complete the web-based CASI in the privacy of their own home. If a subject does not have access to the internet, prefers to complete the BBQ at the study site, or requires assistance in using the CASI, they will be accommodated at the study site.

After completing Visits 1 and 2, eligible subjects will be randomized to one of three groups: 0.1% UC-781 gel, 0.25% UC-781 gel, or a placebo gel (12 per group). A subset of 9 subjects (3 from each group) will also participate in a pK sub-study, which will include 6 timepoints (Visit 3- pre, 0.25 hr, 2 hr, 4 hr, Visit 3A- 24 hr, and Visit 5- 1 day post-QD dose draw). During randomization, study staff will be notified if the participant is randomized to the pK sub-study. Subjects will be randomized in blocks of 3, one per group to minimize imbalance in treatment assignments. The first three subjects enrolled in each of three treatment groups will be selected for the pK sub-study. It is possible that participants may refuse to participate in the sub-study, and spots will continue to be offered as needed.

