## 5.2 Visit 2- Enrollment (Week 0)

### 5.2.1 Non-clinical Procedures

- ⊙ Update locator information and remind participant that he or she will receive visit reminders via email and/or telephone.
- ⊙ Provide test results from screening visit and post-test counseling.  
*If any lab abnormalities ≥Grade 2, subject may not proceed with Visit 2. If the investigator feels that the laboratory abnormalities are transient, the lab tests may be repeated within the visit window. If the repeated labs tests are within normal limits, the subject may proceed with Visit 2 at the discretion of the investigator, the DAIDS Medical Officer, the SMC, and the IRB.*
- ⊙ If subject had a positive STI result at Visit 1, the subject will be referred for treatment of that STI. The subject may proceed to enrollment (Visit 2) one week after a CDC-approved (Appendix X) treatment for the STI.
- ⊙ Collect copy of concomitant medication log
- ⊙ Review precautions listed in Section 5.1.1.
- ⊙ Instruct subject in use of CASI for Baseline Behavioral Questionnaire (BBQ).

Eligible participants who are computer literate will be able to respond to the survey either from their homes or using a terminal at one of the researchers' offices.

Participants who are not computer literate will be given a short tutorial on using the computer to answer questions. When the participant feels comfortable, the research assistant will start the CASI program for the participant. The research assistant will remain in the room while the participant answers the questions but will sit so that he does not see the answers being entered. The research assistant will help with computer questions or problems. If a respondent does not understand a question, the research assistant will read the question aloud, referring to a paper copy of the interview and identifying the question by its number.

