## 5.3 Visit 3- (Week 2 +/- 1 week) Single Dose Administration

### 5.3.1 Non-clinical Procedures

- ⊙ Randomize subject and assign participant ID number prior to Visit Day
- ⊙ Provide test results from Visit 2 and post-test counseling.
 

*If any lab abnormalities ≥Grade 2, subject may not proceed with Visit 3. If the investigator feels that the laboratory abnormalities are transient, the lab tests may be repeated within the visit window. If the repeated labs tests are within normal limits, the subject may proceed with Visit 3 at the discretion of the investigator, the DAIDS Medical Officer, the SMC, and the IRB.*
- ⊙ If subject had a positive STI result at Visit 2, the subject will be referred for treatment of that STI. The subject may proceed to Treatment Stage 1 (Visit 3) one week after a CDC-approved (Appendix X) treatment for the STI.
- ⊙ Update locator information and remind participant that he or she will receive visit reminders via email and/or telephone.
- ⊙ Collect copy of concomitant medication log
- ⊙ Review precautions listed in Section 5.1.1.

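### The baseline questionnaire may be completed at any time before Visit 3, so it can follow the Visit 2 enema and biopsies, which does not fit its stated pre-trial purpose

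*Protocol*

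**What the plan says.** The protocol gives the timing of the BBQ in four places, and they do not agree.

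- Section 2.1.1 gives only an outer limit: "Prior to Visit 3, participants will be asked to respond to the BBQ".
- The Schema and Section 2.2 list the BBQ as part of the Visit 2 baseline evaluation and place randomisation after Visits 1 and 2 are completed. Section 2.2 adds that "acceptability assessments will be completed at baseline and Visit 5".
- Section 5.2.1 (Visit 2) requires instruction in the computer interview but not completion. Computer-literate participants "will be able to respond to the survey either from their homes or using a terminal at one of the researchers' offices".

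Section 5.3.1 sets the time of randomisation: "Randomize subject and assign participant ID number prior to Visit Day", that day being Visit 3.

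On purpose, Table 2 says of the intentions section (I), which covers both a gel and a preparatory enema: "This will allow us to detect pre-trial attitudes about such products and how they may affect later ratings". Sections B and D of the same table ask about usual sexual behaviour, condom use and douching over the prior two months. Section 7.5 takes the BBQ intentions scale as the baseline and forecasts that intention will rise on average through experience of the gel.

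**The concern.** Visit 2 includes a study enema and a sigmoidoscopy with biopsies. A participant who is first shown the computer interview at that visit and then answers at home would normally do so after those procedures. The answers about willingness to use a preparatory enema then come from someone who has just had one as part of the trial, followed by an endoscopy. The douching and behaviour items then include the study enema and a period in which the protocol itself restricts behaviour.

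Two uses of the data are exposed: the before-after change in intention, and the description of what participants usually do. Acceptability is part of the primary objective. A baseline that was not taken at the right time cannot be recovered in the analysis.

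**Working it through.** The protocol gives no figure to reproduce here. The check is a reading of the visit sequence with simple arithmetic.

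**Sequence**

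1. Visit 2 is Week 0 (Section 5.2). The computer-interview instruction is in Section 5.2.1. The enema, lavage and biopsies are in Section 5.2.2: 14 at about 10 cm plus 14 at about 30 cm, so 14 + 14 = 28.
2. Visit 3 is at Week 2 ± 1 week (Section 5.3). The window from Visit 2 to Visit 3 is therefore 2 − 1 = 1 week to 2 + 1 = 3 weeks.
3. Randomisation falls inside that window (Schema, Sections 2.2 and 5.3.1).
4. The first gel dose is at Visit 3 (Section 5.3.2), so every permitted BBQ time precedes gel use.

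**Recall period**

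Section 3.1, criterion 9, asks for rectal abstinence for one week before and one week after each sigmoidoscopy, and for one week before treatment. Take Visit 2 at Week 0 and Visit 3 at Week v, with the BBQ answered just before Visit 3. The required weeks are −1 to 0, 0 to 1, and v − 1 to v. Their total is 2 + min(1, v − 1) weeks, and two months are about 8.7 weeks.

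| BBQ answered | Required abstinence already covered | Share of two months |
|---|---|---|
| On arrival at Visit 2 | up to 1 week | 1/8.7 = 11% |
| Just before Visit 3, v = 1 | 2 weeks | 2/8.7 = 23% |
| Just before Visit 3, v = 2 or 3 | 3 weeks | 3/8.7 = 34% |

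A BBQ answered soon after Visit 2 covers less abstinence than the last two rows, but it already includes the study enema.

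**Change in intention**

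Let g be the effect of using the gel, d1 the shift in intention caused by the Visit 2 procedures and present at a late BBQ, d2 the shift from all study procedures still present at the Product Acceptability Questionnaire (PAQ), and p the share of participants who answer the BBQ after the Visit 2 procedures.

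- All BBQs before Visit 2 procedures: expected change = g + d2.
- All BBQs after: expected change = g + d2 − d1.
- Mixed timing: expected change = g + d2 − p·d1.

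The protocol does not fix p and gives no information on d1 or d2. If d1 is negative, late completion pushes the apparent change upward. If d1 is positive, it pushes it downward.

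**Between arms**

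The Visit 2 procedures are the same for everyone and precede randomisation, and allocation is blinded. The terms d2 and p·d1 therefore have the same expectation in each arm and cancel in a comparison of arms.

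**The case against.** The strongest case on the other side has five parts.

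- **The Schema and Section 2.2 already place the BBQ in Visit 2 with randomisation afterwards.** This stands in part. A reader might infer that the protocol plans for the BBQ after randomisation. That follows only from combining the outer limit in Section 2.1.1 with Section 5.3.1, against two explicit design statements. It is an inconsistency to reconcile, and blinded randomisation alone should not shift answers. Even the tighter reading does not say whether the BBQ comes before or after the procedures within Visit 2.
- **Late completion is permitted, not required.** This stands. Section 5.2.1 precedes the clinical procedures in the text, and completion on site is offered. The baseline may be affected; the protocol does not show that it will be.
- **The affected analysis is narrow.** This stands. The main prediction in Section 7.5 is that the post-use score lies in the top third of the scale, which needs no baseline. The rise from baseline is an additional forecast, and no test for it is specified.
- **A shift could persist.** The PAQ follows a second enema and another 28 biopsies at Visit 3. If the Visit 2 shift is still fully present then (d2 = d1), it cancels, and a late BBQ lies closer to gel use alone. This is correct as algebra, but it needs that equality, which the protocol does not give. It also does not serve the protocol's own stated purpose, a measure of pre-trial attitudes and usual behaviour.
- **Earlier completion does not remove every study contact.** This stands. Visit 1 already includes anoscopy (Section 5.1.2), and the week of abstinence before Visit 2 remains for a BBQ done on arrival.

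**Conclusion.** The point holds in a limited form. The BBQ timing in Sections 2.1.1 and 5.2.1 is looser than in the Schema and Section 2.2, and it allows answers after the Visit 2 enema and 28 biopsies. That does not fit the pre-trial purpose in Table 2. For a BBQ completed just before Visit 3, about 2 to 3 of roughly 8.7 recall weeks fall under required abstinence, if participants keep to criterion 9.

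The within-person change in intention and the description of usual behaviour may be affected. Comparisons between arms and the post-use level prediction are not biased.

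A reader might go further and infer that the study is likely to report a false rise in intention. The protocol does not support this. It would need an assumed fall after Visit 2, an assumed standard deviation, a paired test that the protocol does not specify, and the disappearance of the fall before the PAQ despite the repeated procedures at Visit 3. Neither the size nor the direction of any shift can be derived, so no error rate should be attached to the point.

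**What to change.** Require the BBQ after consent and before any Visit 2 clinical procedure, either at home after Visit 1 or on arrival at Visit 2. It then always precedes randomisation. Move the computer-interview instruction from Section 5.2.1 to Visit 1, replace the Visit 3 limit in Section 2.1.1, and state the same timing in the Schema and Sections 2.1.1, 2.2 and 5.2.1.

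The cost is a wording change and one moved step. Some questionnaires will come from people who are then not enrolled. A BBQ done on arrival at Visit 2 will still follow the Visit 1 anoscopy and up to one week of abstinence, so early completion at home after Visit 1 is the cleaner of the two options.
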